## Assignment of interventions: allocation

### Sequence generation {16a}

To avoid selection bias, an independent statistician will use R software to generate a set of random numbers. The list of random numbers will consist of a set of numbers ranging from the number 1 to the number 78, and they will be randomly divided into intervention group and control group. During the randomization process, the R function "sample ()" will be used to ensure the same group size. The intervention group will be named "Group 1" and the control group will be named "Group 2".

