### Eligibility criteria {10}

The inclusion criteria were: (1) diagnosis of dysphagia according to the Toronto Bedside Swallowing Screening Test (TOR‐BSST); (2) age between 18 and 80 years; (3) no significant cognitive impairment, able to execute instructions correctly, and with Mini-Mental State Examination (MMSE) score ≥ 24; (4) be able to use a computer screen with or without the assistance of others; (5) be able to understand and follow instructions; (6) life expectancy estimated by healthcare providers to be ≥ 12 months; and (7) informed consent to the study can be given by signing an informed consent form.

The exclusion criteria were: (1) dysphagia caused by structural lesions (eg, radiotherapy, previous extensive surgery of the head and neck region such as laryngectomy and cordectomy); (2) combined with serious heart, lung, liver, kidney diseases, and hematological disorders; (3) limb deficiency or paralysis, blindness in both eyes, severe visual impairments; (4) motion sickness or vestibular dysfunction; (5) history of epilepsy, malignancy or other neurological diseases; or (6) pregnancy or breastfeeding. Some of the exclusion criteria depended on the video-game device or were precautions designed to not harm participants after using video-game technology. Because of the need to use video games, there is concern that people over the age of 80 will not be able to use computers or view electronic screens, thus limiting participants under the age of 80.

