### Outcomes {12}

All assessments were completed by an experienced occupational therapist who was blind to the participants' group assignments. Assessments were conducted before the start of the intervention (pre-training), after 4 weeks of treatment (post-training), and at the 1-month follow-up (follow-up).

The primary outcome of this study was swallowing function, assessed using the Toronto Bedside Swallowing Screening Test (TOR-BSST) and the Functional Oral Intake Scale (FOIS). The Toronto Bedside Swallowing Screening Test (TOR‐BSST) is the best performing water swallow screening tool [21] with a sensitivity of 91.3%, a negative predictive value of 93.3% in the acute phase and 89.5% in the recovery phase [22]. TOR-BSST has shown to be more convenient and cheaper in bedside screening compared to the gold standard method of simultaneous videofluoroscopy (VFSS), which is an invasive assessment. Due to the limitations of the experimental site, we chose TOR-BSST as the assessment tool for dysphagia. FOIS consists of a 7-point scale, with level 1 indicating completely impaired oral intake and level 7 indicating complete oral intake regardless of food concentration or type [23].

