### Recruitment {15}

All patients with dysphagia who meet the inclusion criteria are eligible to participate. The study will recruit patients at the rehabilitation center by distributing posters and leaflets containing information about the study. We will collaborate with doctors and rehabilitation therapists, request their help in promoting publicizing the study after the clinic treatments. In addition to this, we will actively promote the study to patients in the wards.

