### Methods for additional analyses (e.g. subgroup analyses) {20b}

N/A: No subgroup analyses or adjusted analyses will be performed because they are not part of the planned analyses for this study. The primary analysis is sufficient to address the research question.

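### Time since onset is left uncontrolled at entry, allocation and analysis; this gives up some precision, and one pre-specified adjusted model would recover it

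*Protocol article*

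**What the plan says.** **Entry.** Eligibility criteria {10} requires "diagnosis of dysphagia according to the Toronto Bedside Swallowing Screening Test" and puts numerical limits on age, cognition and life expectancy. Nothing bounds time since onset. The exclusions, such as "history of epilepsy, malignancy or other neurological diseases", restrict cause or history, not duration. Recruitment {15} states that "All patients with dysphagia who meet the inclusion criteria are eligible to participate". Patients are approached through posters and leaflets, after clinic treatment and on the wards ("we will actively promote the study to patients in the wards").

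**Allocation.** Sequence generation {16a} describes one list numbered 1 to 78: "they will be randomly divided into intervention group and control group". The R function is used so that the two groups are of equal size. No stratification factor is named. Under Implementation {16c}, the envelope is opened after consent and the baseline assessment.

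**Analysis.** The between-arm methods in section {20a} (t or rank-sum tests, repeated-measures ANOVA, a mixed model if normality fails) name no covariate. Section {20b} then closes the route: "No subgroup analyses or adjusted analyses will be performed because they are not part of the planned analyses".

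**The concern.** If patients early after onset recover more over 4 weeks than long-standing cases, whatever training they receive, the FOIS result depends on time since onset as well as on the arm. A trial can deal with such a factor by narrowing entry, balancing allocation or adjusting the analysis. This plan does none of the three, and it excludes the third explicitly, so the gap is not a detail left to a fuller document.

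Two things are at stake. The spread in natural recovery stays in the error term and widens the confidence interval. And if chance puts more early patients in one arm, the primary result carries that imbalance, with no planned analysis that could take it out.

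**Working it through.** **1. The plan's own figure.** Sample size {14} gives FOIS means of 5.40 and 4.40 and SDs of 1.70 and 0.80.

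- Planning variance = (1.70² + 0.80²)/2 = 1.765; SD = 1.329; standardised difference = 1.00/1.329 = 0.753.
- With 31 per arm, the noncentral t gives power of 90% for a one-sided 0.05 test and 83% for a two-sided one. The stated 31 therefore reproduces as a one-sided calculation. Sidedness is a separate matter; two-sided figures are used below.
- 31/(1 − 0.20) = 38.75, rounded up to 39 per arm, or 78 in total. This reproduces.

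**2. Assumptions (not in the documents).** Share of early patients *p*: about 10% (8 of 78) to 50% (39 of 78). Extra 4-week recovery in early patients, equal in both arms, *g*: 0.5 to 1.5 FOIS points.

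**3. Chance imbalance under one 39:39 list.** The number of early patients in one arm is hypergeometric. The SD of the difference in shares is 2 × √[39 × p(1 − p) × 39/77] / 39.

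- 39 of 78 early: SD 0.114; P(difference ≥ 7/39, or 18 points) = 0.174.
- 8 of 78 early: SD 0.069; P(difference ≥ 6/39, or 15 points) = 0.056.
- The shift in the estimate is imbalance × *g*. A one-SD imbalance shifts it by 0.069 × 0.5 = 0.03 to 0.114 × 1.5 = 0.17 points. The planned effect is 1.0, and the standard error at 39 per arm is 1.329 × √(2/39) = 0.30.

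**4. Share of the planning variance.** Share = p(1 − p)g²/1.765, with p(1 − p) = 0.092 for 8 of 78 and 0.25 for 39 of 78. The last two columns give two-sided power at 31 per arm across that range. The reference value is 83%.

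| Gap *g* | Share, 8 of 78 | Share, 39 of 78 | Adjusted, if 1.329 already contains this spread | Unadjusted, if the spread comes on top of 1.329 |
|---|---|---|---|---|
| 0.5 | 1.3% | 3.5% | about 84% | 82–83% |
| 1.0 | 5.2% | 14.2% | 85–88% | 78–81% |
| 1.5 | 11.7% | 31.9% | 87–94% | 72–79% |

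The two power columns are alternative readings. In the first, the plan keeps its 83% and forgoes a gain. In the second, it falls below 83%, and adjustment restores it.

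**5. Stratification or adjustment?** This was simulated with 62 completers, half of them early, the spread on top of 1.329 and a two-sided 0.05 test (10,000 runs per scenario). At a gap of 1 point, power was 78% as planned, 83% with adjustment alone, and 83% with stratification plus adjustment. At 2 points, beyond the range above, the figures were 65%, 82% and 82%. Type I error was 4.7–5.3% throughout, and the mean estimate matched the true effect.

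**The case against.** A reader might infer that the trial could systematically credit spontaneous recovery to the game. The documents do not support that. The control arm is concurrent and randomised and, by the plan's account, receives the same programme components for the same time, so natural recovery cancels on average. Chance imbalance is already reflected in the standard error and the p-value. The simulation shows neither bias nor an inflated type I error.

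A reader might also take "a negative predictive value of 93.3% in the acute phase and 89.5% in the recovery phase" in Outcomes {12} as evidence that acute patients will be enrolled. That phrase describes the screening test's performance. The setting is a rehabilitation center, and recruiting from both its wards and its clinic does not establish a mix of phases. The phase mix and the recovery gap remain assumptions.

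Three further objections carry weight. If the earlier study's SDs came from patients of mixed duration, N = 78 already allows for this spread and there is no shortfall against plan. A single equal-size list is a valid method for one center and 78 patients, and step 5 shows that stratification adds almost nothing beyond adjustment. Broad entry is a legitimate choice for the investigators. What stands is narrower: section {20b} forbids a simple analysis that could only help precision, and gives no reason beyond its not having been planned.

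**Conclusion.** The point holds as a minor and inexpensive improvement. It is not a flaw in validity. Entry, allocation and analysis together leave time since onset uncontrolled; the cost is precision, plus a realised imbalance that could not be corrected. The benefit is negligible at a recovery gap of 0.5 FOIS points. At 1.0 point, adjustment raises two-sided power at 31 per arm from 83% to 85–88% if the planning SD already contains the spread. If it does not, adjustment recovers a fall to 78–81%. The documents do not settle which reading applies. All these sizes rest on the assumed early share of 10–50% and on a gap that is the same in both arms.

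**What to change.** Before recruitment starts:

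1. Record time since onset at the baseline assessment, which already precedes allocation under Implementation {16c}. The schedule table is not shown, so the item may already be there.
2. Amend sections {20a} and {20b} so that the between-arm FOIS model pre-specifies adjustment for time since onset and for baseline FOIS, which is already collected. State how time since onset enters the model (continuous or categorised) and how patients without a datable onset are handled.
3. Optionally, stratify the list in section {16a} by a time-since-onset cut-off fixed in advance, with varying block sizes and one envelope series per stratum.

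Steps 1 and 2 cost one extra baseline item, a covariate that may be hard to date where onset is gradual, and a short amendment. Step 3 adds slightly unequal arm sizes and somewhat more predictable allocations, which matters because therapists are not blinded. No additional patients are needed, and the eligibility criteria need not change.

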### Intervention description {11a}

#### Instrumentation

A video-game based swallowing exercise was developed by our team, consisting of a computer screen, and a facial recognition device. To ensure the patient-centered design of video-game, we adopted the TURF (Task, User, Performance, and Function) unified usability framework [19]. In TURF, usability refers to "the usefulness, usability, and satisfaction of the target user in achieving the goals of the work domain by performing certain sequences of tasks". This framework was developed for healthcare settings and is often the basis for ensuring good usability in design. Participants will face a computer and a facial recognition device, which is constructed from a facial landmark detector in the MediaPipe Artificial Intelligence model library. It will generate the 3D positions of 468 facial feature points on the facial images, including information about cheeks, mouth, chin and other facial areas [20]. Through changes in the 3D position of facial feature points, changes in facial muscles and expressions of participants will be detected, and the computer obtains biofeedback through real-time game-controlled computation.

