## Assignment of interventions: blinding

### Who will be blinded {17a}

The evaluator will blind to the assignment of all participants, and will not participate in the application of the treatment or the statistical analyses. Due to the specific nature of video-game interventions, it is not possible to blind participants and therapists.

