### Procedure for unblinding if needed {17b}

N/A: Only outcome evaluators in this study will be blinded, so unblinding will not occur.

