### Confidentiality {27}

All data in this study will be anonymized and strict confidentiality measures will be taken. Access to participant data will be restricted to authorized members of the research team and the Ethics Committee of The Hong Kong Polytechnic University. To enhance participant confidentiality, each participant will be provided with a unique trial identification number and his/her details will be securely stored in a protected database at The Hong Kong Polytechnic University. Access to the dataset will be strictly controlled and will only be granted to the research team and the sponsoring organization. It is important to note that participant identification details will not be reported in any publications or studies. In addition, the possibility of sharing anonymized trial data with other researchers for international prospective meta-analyses will be carefully considered, and appropriate measures will be taken to protect participant privacy and confidentiality, such as thoroughly de-identifying all direct identifiable information of participants before data sharing, and processing indirect identifiable information that may contain sensitive information, such as date of birth, by keeping only the year or age, in order to protect the privacy and confidentiality of participants.

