## Statistical methods

### Statistical methods for primary and secondary outcomes {20a}

An intention-to-treat analysis will be performed, and the last available measurement will be used when data were lost due to dropout. Statistical analysis will be performed using SPSS 29.0. Statistical significance of all outcome variables will be established at *P* < 0.05.

All continuous data will be tested for normality, and nonparametric tests will be used for non-normally distributed data. Data conforming to normal distribution will be expressed as mean ± standard deviation (SD), and data with non-normal distribution will be expressed as median (interquartile range).

Comparisons of continuous data of two groups at the same time will be analyzed using independent samples t tests or rank sum tests, and comparisons of two groups of rates will be performed using chi-square test or Fisher exact test [31].

Comparison of continuous data trends over time between different groups at different times, if data normality is present, we will perform a series of repeated measures analysis of variance (ANOVA) for each outcome measure to assess differences between time (4 weeks and 1 month post) and between study groups, as well as interactions between time and study groups. For these analyses, the assumptions of sphericity and homogeneity of variances are tested using Mauchly and Levene tests [32]. If the assumption of sphericity is violated, the Huynh–Feldt correction is applied [32].

If the normality assumption is not met, the linear mixed model will be used for analysis, the comparative analysis at each time was performed using the nonparametric statistical Mann–Whitney U test and its own control two-way comparison using the nonparametric statistical Kruskal–Wallis rank sum test [33].

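### The plan leaves the analyst unblinded while the choice of test and the handling of missing data are still open; a neutral code in the analysis file would cost almost nothing

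*Protocol article*

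**What the plan says.** **Who is blinded.** Procedure for unblinding if needed {17b}: "Only outcome evaluators in this study will be blinded, so unblinding will not occur". Who will be blinded {17a} adds that the evaluator "will not participate in the application of the treatment or the statistical analyses". Trial design {8} calls the trial single-blind.

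**What the labels mean.** Sequence generation {16a}: "The intervention group will be named 'Group 1' and the control group will be named 'Group 2". The same section gives the list to an outside person: "an independent statistician will use R software to generate a set of random numbers". It states no analysis role for that person.

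**Who could be the analyst.** Instrumentation, under {11a}: "A video-game based swallowing exercise was developed by our team". Under Confidentiality {27}, access to the dataset "will only be granted to the research team and the sponsoring organization". No section names the analyst.

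**What is left to the data.** Statistical methods {20a}: "All continuous data will be tested for normality, and nonparametric tests will be used for non-normally distributed data". It names no normality test and no cut-off. For trends over time, repeated-measures ANOVA applies under normality, and otherwise: "If the normality assumption is not met, the linear mixed model will be used for analysis", with rank tests alongside.

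**Missing data.** Both {20a} and {20c} carry the last measurement forward after dropout. Section {20c} then also prescribes multiple imputation and does not say which method is primary.

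**The concern.** An unblinded analyst does little harm when a single analysis is fixed in advance. Here some decisions come after the data are in: whether a distribution counts as normal, and therefore which test and model apply, and which missing-data method supplies the main result. Someone who knows which arm is the game can see which option favours it, and the judgement can drift that way without any intent. Patients and therapists cannot be blinded in this trial, so the analysis is one of the few remaining places where masking is possible.

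This is not mere silence that a statistical analysis plan could fill. Section {17b} makes an affirmative statement that only evaluators are blinded, and an analysis plan that masked the analyst would contradict it.

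**Working it through.** **1. Is the analyst unblinded under the plan?** Section {17b} limits blinding to outcome evaluators, and {17a} removes the evaluator from the analysis. No blinded person is left to analyse. The independent statistician of {16a} would not be masked either, having produced the list for numbers 1 to 78.

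**2. Which choices are open?** (a) t test or rank-sum test; (b) ANOVA or mixed model with rank tests; (c) last observation carried forward or multiple imputation. Choices (a) and (b) depend on an undefined normality check. Choice (c) has no stated order.

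**3. How much can these choices move the error rate?** The protocol gives no figure on this point. A null simulation was run with 6,000 trials, 39 per arm (78/2), a score rounded to 1-7, 20% dropout and nominal 5%. The score model and the random dropout are assumptions.

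| Rule | Significant |
|---|---|
| t test only | 4.5% |
| Mann-Whitney only | 4.6% |
| Shapiro-Wilk rule applied mechanically | 4.6% |
| Better of t and Mann-Whitney | 5.1% |
| Best of both tests, across carry-forward and complete cases | 7.4% |

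Complete cases stand in for multiple imputation. The Monte Carlo standard error at 5% is √(0.05 × 0.95/6000) = 0.28 percentage points. The normality choice alone therefore shows no inflation, while adding the missing-data choice does.

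**4. How much of this does masking remove?** By symmetry, a masked analyst who reports the smallest P value reaches the same 7.4%, with half of it (3.7%) favouring the game. Masking does not reduce the number of analyses. In a wider set (two visit-wise t tests, the ANOVA group effect and the interaction; 39 per arm; visit correlation 0.5-0.7), false significance favouring the game was about 6.0-6.5% masked and 6.3-6.9% unmasked.

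**5. What masking does remove is direction.** Take two null statistics X and Y, approximately standard normal with correlation r. An analyst who always keeps the one more favourable to the game reports on average

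E[max(X,Y)] = ½E|X−Y| = √((1−r)/π).

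- r = 0.5: √(0.5/π) = 0.40
- r = 0.7: √(0.3/π) = 0.31

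A masked analyst who keeps the larger absolute value reports 0 on average, by symmetry. These correlations describe two visits. Two missing-data methods applied to the same data would agree more closely. If r = 0.8 to 0.95 is assumed, the lean is √(0.2/π) = 0.25 down to √(0.05/π) = 0.13.

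**6. In FOIS points.** Sample size {14} gives SDs of 1.70 and 0.80, so the root-mean-square SD is √((2.89 + 0.64)/2) = 1.3285. With 39 per arm, the standard error of the difference is 1.3285 × √(2/39) = 0.301. A lean of 0.13 to 0.25 is about 0.04 to 0.08 points, against a planned difference of 5.40 − 4.40 = 1.00.

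**The case against.** The strongest reply is that masking changes little. A masked analyst sees the same P values, and the gain in false significance is about 0.3-0.4 percentage points. Most of the protection comes from fixing the analysis in advance. This stands, and it limits the point to a minor one and adds prespecification to the fix. It does not remove the point, because masking also takes away the directional lean.

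Four stronger readings are tempting, and the document does not support them.

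- **The game's developers analyse their own product.** A reader might infer this from {11a} and {27}. Those sections say who built the game and who may see the data, not who runs the tests. The protocol permits the arrangement but does not state it.
- **Naming the groups is itself the fault.** Under Implementation {16c}, participants are assigned by the number in the envelope, so staff need a key. Nothing says that the analysis file must carry the same labels. The exposure comes from {17a} and {17b}.
- **Unblinding raises the false-positive rate to 12-14%.** That is roughly the chance that at least one of the four FOIS tests in step 4 is significant under no effect. The visit-wise comparisons and the ANOVA are all planned, so the figure measures multiplicity, which a masked analyst faces equally.
- **Masking would cure the patient-replacement rule in {11b}.** That decision is taken during the trial, where participants and therapists know the arms. Recoding a file cannot reach it.

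**Conclusion.** The point holds in limited form. Sections {17a} and {17b} together leave the analyst unblinded, while {20a} and {20c} leave open the normality-based choices and the missing-data method. The likely effect on false significance is small. The directional lean is at most a few tenths of a standard error, and about 0.04 to 0.08 FOIS points for the choice of missing-data method. These sizes assume no true effect, 39 per arm, the correlations stated above and an analyst who always takes the favourable option, so they are upper limits for each scenario and not forecasts. The documents do not show that anyone would behave this way. This is a cheap improvement of minor weight, and the sample size is unaffected.

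**What to change.** - Amend {17a} and {17b} so that the analyst is listed among the blinded roles.
- Give the analysis file a neutral random code (A/B) in place of Group 1 and Group 2. The labels in {16a} may stay for allocation.
- Have the independent statistician of {16a} hold the key, without doing the masked analysis, until data cleaning, the choice of test, the missing-data handling and the primary results are locked.
- Fix one primary model and one primary missing-data method in {20a} and {20c} before data are seen, and label the other missing-data method as a sensitivity analysis. Masking cannot do this part.

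**Cost.** Mainly wording, plus one recoding step by a role the trial already has. Trial status describes this version as pre-recruitment, so the change can precede any data. There is one small downside. Items that reveal the arm must stay out of the masked file, notably satisfaction, which {12} and {18a} describe in terms of the video game. The per-protocol analysis in {20c} is worded for non-adherers in the intervention group, so it would have to wait until the key is opened.
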